#### **Specific Aim 4 (Business-Case) Analysis:**

For the business-case analysis, we will evaluate the effect of the intervention on annual patient-level healthcare costs after index admission, while adjusting for annual patient-level healthcare costs prior to admission. To do this, we will include 7-month data periods that occur during baseline and active implementation. Costs will first be converted to the same fiscal year to account for inflation using the Consumer Price Index (CPI). The basic stepped wedge model will be fit using a generalized linear mixed model approach assuming the costs follow a gamma distribution with log link. Model results will be evaluated to check assumptions. The model will include the prior annual healthcare costs as a covariate, time period (as categorical), and active implementation indicator. Additionally, a random site-level intercept will be included to account for any heterogeneity in costs due to unmeasured site-level factors. Some patients may die within 12 months of the index admission and other patients in the last wave of sites may have fewer than 12 months of cost data available due to administrative cutoff of the database. This information will be examined descriptively. Initial models may only use patients with complete cost information available. Alternatively, we will consider treating costs as right censored for those with incomplete information.

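### The Aim 4 cost analysis treats death within 12 months like database cutoff, and neither handling it names is right for patients who die

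*Protocol*

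**What the plan says.** All of the following is in the Protocol, section 5.7.3, under the Specific Aim 4 (Business-Case) Analysis heading, unless another place is named.

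- **Aim.** The analysis will "evaluate the effect of the intervention on annual patient-level healthcare costs after index admission", adjusting for cost in the year before.
- **Phases.** For this, "we will include 7-month data periods that occur during baseline and active implementation". The sustainability periods are left out, and the business-case overview limits cost data to the six ASAP sites.
- **Model.** A gamma model with log link, with prior annual cost, categorical period, an active-implementation indicator and a random site intercept.
- **Why a year may be incomplete.** "Some patients may die within 12 months of the index admission", with no limit to one phase. In addition, patients in the last wave may lack a full year because the database ends.
- **What will be done.** "This information will be examined descriptively". Then: "Initial models may only use patients with complete cost information available". Then: "Alternatively, we will consider treating costs as right censored for those with incomplete information".

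No sentence separates the two reasons when the handling is described. No sentence says that a death completes the cost record. No cutoff date and no method for censored costs are given.

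**The concern.** The two kinds of incompleteness differ. A patient alive when the database ends has costs still to come that are not seen. A patient who dies in month 4 has no further costs, so the 12-month total is fully known.

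Deleting deaths restricts the comparison to 12-month survivors. That is selection on something the programme is meant to change: section 2 (Specific Aim 1) puts all-cause mortality inside the 90-day event composite, hypothesised at 3.5% under intervention vs 10% for controls. The Aim 4 hypothesis is itself that savings come from fewer recurrent events. Censoring deaths instead makes the model supply spending after death.

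At stake is the cost difference between intervention and usual-care patients. The business-case overview lists it as part of the final product of Aim 4, and the abstract says the results will be shared with facility leaders who may adopt the programme.

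**Working it through.** **Reproducing the protocol's own figure.** Aim 4 states no sample size. The only usable figure is the number of patients per site per 7-month period in the diagnostic-rate power section: 111 × 7/12 = 64.75, stated as approximately 64. It reproduces.

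**Step 1. Deaths under complete-case analysis.** Set mean survivor cost to 1 in both phases, so the programme has no effect on survivors' costs. Let decedents cost k times survivors in both phases, and let 12-month mortality be d0 (baseline) and d1 (active).

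- True cost ratio = [(1 − d1) + d1·k] / [(1 − d0) + d0·k]
- Survivor-only ratio = 1.00 by construction

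The protocol gives no mortality rate and no k. I assume d0 = 10% and d1 = 3.5%, borrowing the hypothesised 90-day composite figures as a scale for 12-month mortality. A second assumed pair is 15% vs 10%.

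**Step 2. Deaths under simple right-censoring on the cost scale.** Take the simplest gamma case, shape 1 (exponential). The censored-data estimate of a group's mean is total observed cost divided by the number uncensored: [(1 − d) + d·k] / (1 − d). Each group's true mean is therefore inflated by 1/(1 − d), and the ratio is multiplied by (1 − d0)/(1 − d1) whatever k is:

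- 10% vs 3.5%: 0.90/0.965 = 0.933
- 15% vs 10%: 0.85/0.90 = 0.944

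| d0, d1 | k | True ratio | Survivors only | Deaths censored |
|---|---|---|---|---|
| 10%, 3.5% | 0.5 | 0.9825/0.950 = 1.034 | 1.00 | 0.965 |
| 10%, 3.5% | 1 | 1.000 | 1.00 | 0.933 |
| 10%, 3.5% | 2 | 1.035/1.100 = 0.941 | 1.00 | 0.878 |
| 10%, 3.5% | 3 | 1.070/1.200 = 0.892 | 1.00 | 0.832 |
| 15%, 10% | 0.5 | 0.950/0.925 = 1.027 | 1.00 | 0.970 |
| 15%, 10% | 1.5 | 1.050/1.075 = 0.977 | 1.00 | 0.922 |
| 10%, 10% | any | 1.000 | 1.00 | 1.000 |

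In these cases complete-case analysis hides a saving when decedents are costly and hides an increase when they are cheap. Censoring pushes the ratio towards a saving, and at k = 0.5 it turns a cost increase into an apparent saving. With equal mortality and equal k, neither handling biases the ratio.

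**Step 3. Whom the cutoff reaches.** Figure 1 is not shown, so I assume a layout that fits the eight 7-month periods of section 5.7.b and the wave description in section 5.1.a: active periods 4–6 (Wave 1), 5–7 (Wave 2) and 6–8 (Wave 3). The last baseline period then ends 21 months before period 8 ends, so cutoff cannot reach baseline patients. At 111 patients per site-year there are 6 × 21 × 111/12 ≈ 1,166 active patients. Those with under 12 months of follow-up are:

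| Data end after period 8 | Wave 2 | Wave 3 | Share of active |
|---|---|---|---|
| 0 months | 5 of 21 months, about 93 | 12 of 21 months, 222 | 27% |
| 5 months | 0 | 7 of 21 months, about 130 | 11% |
| 12 months | 0 | 0 | 0% |

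The protocol attributes cutoff to the last wave only. Under this layout that means data running at least 5 months past period 8, so a loss of at most about 11%.

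**Step 4. Does deleting cutoff patients bias the pooled estimate?** I used a linear analogue of the planned model (categorical period, active indicator, random site intercept, six sites, no sustainability periods), with data ending at period 8, the worst case.

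- Period 8 holds only Wave 3 active patients, so its net weight on the effect is 0.
- In period 7 both contributing waves are active, with weights of about −0.05 to −0.07 and +0.05 to +0.07 that cancel.
- The complete-case standard error is 1.003 to 1.004 times the full-data one for intra-cluster correlations from 0.01 to 0.2.
- A constant effect is estimated without bias. If the effect varies with exposure time, the estimate moves by about 0.02 of the maximum effect (for example 1.089 to 1.071).

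**Step 5. Single-site business cases.** Section 5.7.3 also plans an analysis at each site if staff-time data allow. In a before-after comparison at one site no other wave offsets the loss. If data end with period 8, a Wave 3 site keeps 9 of its 21 active months, and 7 of those 9 are the start-up period that the Aim 1 sensitivity analysis tests leaving out. With six more months of data it keeps 15, of which 7 are start-up. With twelve more it keeps all 21.

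**The case against.** The strongest reply is that nothing is fixed. The complete-case option is introduced with a may and the other with an intention to consider: "we will consider treating costs as right censored for those with incomplete information". Incompleteness is to be described first, and an SAP that is not shown may settle the method. This stands against saying that the analysis will drop patients, and it lowers the severity. It does not remove the point. These are the only handlings the protocol names, and it applies both to deaths and cutoff without distinction.

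It is also fair that inverse-probability-of-censoring weighting is itself a method for right-censored costs. For patients alive at cutoff, the protocol's second option could be carried out properly. For deaths it could not, because a death is not censoring of cost.

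A reader might go further and infer that both options remove late intervention patients only, and so bias the business case through the cutoff. The documents do not support that. Right-censoring removes nobody. Complete-case analysis also drops baseline patients who die. The text confines cutoff to the last wave, so Wave 2 losses and a 27% loss need an assumed early end of data. Step 4 shows that cutoff deletion barely moves the pooled estimate.

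**Conclusion.** The point holds for deaths. Section 5.7.3 puts death and database cutoff in one class of incomplete cost data, and neither named handling treats a death as the complete record it is.

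The size cannot be derived from the protocol. Under assumed 12-month mortality of 10% vs 3.5%, decedents costing 0.5 to 3 times survivors, equal relative decedent cost in both phases and unchanged survivor costs, the true ratio lies between 1.03 and 0.89 while survivors alone show 1.00. The direction depends on whether decedents cost less or more than survivors. The censoring figures rest further on the exponential special case.

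For cutoff, no material bias in the pooled period-adjusted estimate is shown, given the assumed wave layout and the linear analogue of the gamma model. It remains a possible problem for single-site business cases at Wave 3 sites. This is worth correcting, but it concerns the fourth aim and provisional wording, not the primary outcome.

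**What to change.** In the Specific Aim 4 (Business-Case) Analysis text, separate the two cases.

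1. **Death within 12 months.** State that this is complete follow-up: annual cost is cost to death and zero afterwards. Keep these patients in every cost model, including the initial ones.
2. **Alive at database cutoff.** For these patients only, use partitioned (monthly) costs or inverse-probability-of-censoring weights. Do not apply simple censoring on the cost scale: patients who spend faster are censored at higher cost, so the censoring is informative even when the cutoff date is not.
3. **Single-site analyses.** Use the same handling and report how many of each site's active months have a full year of cost data.

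The change uses data already to be extracted. It costs a little more analysis work and slightly more complex reporting.

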#### **5.7 Withdrawal of Subjects**

The patients do not actively enroll or withdraw from the study. If they meet the exclusion criteria, their data will not be included in the analyses.

Health care providers and administrators who are invited to participate in the study will always have the right to withdraw from the study at any time without repercussions.

### **4. Reporting**

Assessment of level of risk: minimal

Oversight for this investigation will be provided by: Drs. [name] (PI) and [name] (PI)

Internal Data Monitoring Committee (DMC): Will be comprised of Drs. [name] and [name] and the quantitative core (Drs. [name] and [name]). This DMC will meet at least quarterly and more regularly should concerns arise regarding data integrity. Note: reporting to the VA HSRD DMC will occur as required by that committee (anticipated to be annually).

Monitoring of Adverse Events and Safety Plan: Participants (specifically VHA Employees) will be monitored regularly for adverse events by the Program Coordinator. Staff members are trained to report any adverse events (AEs) promptly to the PIs. Participants will be encouraged to report any adverse events they have experienced. We anticipate that using this active identification method will allow us to identify all adverse events in a timely manner. Based on our prior experience with implementation trials, we do not anticipate that any participant will experience adverse events related to participation other than the expected inconvenience related to scheduling time for interviews, Kick-Off, and quality

improvement meetings. The Program Coordinators will be responsible for reviewing the adverse events reporting of all participants each day and reporting the information to the PIs.

Reporting of Unanticipated Problems or Adverse Events: As per VHA rules, we will notify the IRB promptly using the appropriate form when any serious adverse event occurs. If the incident is serious unanticipated or requires revision of the Project Description we will notify the IRB by telephone as soon as possible and always within 24 hours. A formal report will be provided within 2 business days. All adverse events will be reported yearly to the IRB for review regardless of seriousness or relationship to the research. Because of this policy, the IRB will be providing parallel review of adverse events along with the PIs. We believe this will insure stringent oversight and early identification of any unexpected risks to human subjects.

Accuracy and Integrity of the Data: Will be ensured in three ways. Firstly, the VA Connecticut Healthcare System and Richard L. Roudebush VAMC Centers for Health Services Research conduct computer operations in its secure Centralized Computing Facility managed by VHA OI&T network and server administrators. In each Center's computing facility, all research data are stored on VHA-Administered servers which are physically secured in either West Haven, CT, or Indianapolis, IN, VAMC computer rooms. VHA network access to research data is controlled in accordance with the Center's Standard Operating Procedures and VA policies and in cooperation with the VA Connecticut Healthcare System and Richard L. Roudebush VAMC IRBs. In addition, standard operating procedures have been developed to ensure servers, workstations and portable computers are kept up-to-date with virus filters, security patches, software updates and firmware updates. Secondly, the project coordinators will review a sample of the interviews to ensure adherence to the study protocol. Thirdly, a 10% random sample of all charts will be double abstracted to examine inter-rater variation. Variables with discrepancies will be reviewed by the whole chart review team to identify potential problems with the data collection tool or the data dictionary.

## **5. Privacy and Confidentiality**

The ASAP program is an inherently low-risk project. The primary risks relate to the unauthorized release of study-related patient or staff information. Potential risk is characterized as not greater than minimal, that is, a degree of risk that is no greater than that encountered during daily activities. Participation in the study is not anticipated to be associated with any substantial discomfort or inconvenience. There is a small risk to subjects of loss of privacy or confidentiality.

All project staff members are professionals with extensive training related to required procedures for maintaining confidentiality and privacy. Additionally, specific efforts will be maintained to maximize the likelihood that research related information will be kept secure and unavailable to others not involved in the project. As described above, only a code number will identify research records. The code number will not be based on any information that could be used to identify a participant (for example, social security number, initials, birth date,

etc.). The master list will be kept separately from the research data and stored as an electronic data file behind the VA firewall. Only authorized persons will have access to the information gathered in this project. There is little risk to loss of privacy or confidentiality given these measures, and there has been no instance of a problem in this area in prior trials conducted by this investigative team.

In considering risks pertaining to confidentiality, the following safeguards will be in effect in ASAP:

1) Data Confidentiality – We have standard operating procedures for data acquisition and data management. These procedures were designed to protect against data loss and maintain patient confidentiality. These procedures have been developed and used in many studies and we will adhere to these procedures for the proposed study. Audio files and transcriptions related to interviews will be stored behind the VHA firewall on a secure VA-server. Computer files will be password protected. Files containing names or other personal identifiers will have a separate password and will be accessible only to personnel who need to contact subjects.

2) Breach of confidentiality – All participant information collected in the context of this research study, and even the fact that an individual is participating in the study, will be considered confidential. This confidentiality will be assured through several mechanisms. First, each participant will be assigned an anonymous study ID.. In addition, such materials, when in use, will be kept away from public scrutiny. Third, access to all participant data will be restricted to authorized personnel. In the case of computerized study data, access to data will be password protected, and staff members will be assigned individualized passwords that allow them access to only those elements of the data management system to which they are authorized. In addition, all study personnel will maintain certification with training in research ethics, which includes training on confidentiality. Finally, participants will not be identified by name in any reports or publications, nor will data be presented in such a way that the identity of individual participants can be inferred. All information obtained within the course of the study that identifies an individual will be treated as confidential in accordance with section 903C of the Public Health Service Act (42 U.S.C.299a-1). We will remove all identifiers from analytic data sets after data merging and keep all personal identifiers in a separate location from the analytic data. All research data files are organized by study ID number and have no names or other identification attached. This ID number links all computerized research records.

3) Data Security – We have developed standard operating procedures for data management in the conduct of previous trials. These procedures were designed to protect against data loss and maintain participant confidentiality. The study team will take steps to ensure the participant's confidentiality is protected at each step of the process. As stated above, participant will be assigned unique ID numbers (unrelated to their social security numbers or other identifiers). Our study data will be maintained on VHA network servers which are secured and

backed-up on a nightly basis. Access to these servers is controlled by network administrators.

4) Digital Audio Recording of VHA Employee and Veteran Interviews – Audio taping is necessary to ensure that all information during the interviews is collected. Participants who decline will not be eligible to participate in the interviews. Participants will be asked to provide verbal consent. They will also be asked to state their consent to audio recording of the interview at the beginning of the interview as soon as the recorder is turned on. The digital audio recording will be labeled with the subject's project ID# and will not contain any identifying information. Only approved research personnel will have access to the audio files, and they will be stored behind the VHA firewall.

## **6. Communication Plan**

[name], in conjunction with VA Connecticut Healthcare System and Richard L. Roudebush VAMC ASAP staff, will communicate with the Local Site Investigators (LSIs) and site-based ASAP staff regarding obtaining local site approvals. Staff within the two research coordinating centers will aid each site in completing requisite approvals. During the kick-off at the start of each wave for each site, ASAP-staff and the LSI will agree upon a schedule of meetings, which will include a scheduled meeting (likely once/month) and how best and when to convene ad hoc meetings. Calling an ad hoc meeting may be prompted based on the data monitoring where there is an unfavorable mismatch between the number of patients admitted who were eligible for the ASAP protocol and those who received it. For example, a site may have had 15 Veterans admitted who could have benefited from the ASAP protocol, whereas only 3 Veterans received it. In this example, the mismatch may be because of logistical concerns implementing the project or because the site where research is being conducted is not fully engaged. ASAP personnel will communicate about these concerns and, as necessary, perform a Plan-Do-Study-Act (PDSA) to determine how to improve implementation of the ASAP protocol. Should it be determined that a given site is not engaged in the project, Drs. [name] and [name] will communicate with the Director to provide notification and to seek guidance on next steps.

In order to keep all 6 engaged intervention sites informed of changes to the protocol, informed consent, and/or HIPAA authorization, Drs. [name] and [name] will send emails out to the LSI and appropriate local staff (e.g., site-based research assistants) regarding upcoming changes as well as the most updated forms. Should questions arise regarding updates, [name] has the contact information (including email addresses, VA-office phone number, and cell phone numbers) of each LSI. As such, an ad hoc meeting could be convened to discuss changes. Additionally, announcements regarding any changes will also be made on the Systems Redesign Virtual Collaborative/IOP. These same lines of communication will also be used to inform local sites of any serious adverse events, unanticipated problems, and/or interim results which may impact the conduct of the study. Sharing unanticipated problems as well as possible solutions is an important component of our Systems Redesign Virtual

Collaborative/IOP which will allow for sites to learn from one another and from interim study results.

In order to ensure that the study is conducted according to the IRB-approved protocol, ASAP study coordinators from VA Connecticut Healthcare System and Richard L. Roudebush VAMC will assist with reporting to VA Central IRB and each local VA research service regarding study progress. If a potential protocol violation has occurred, either as reported by an LSI and/or discerned during the course of chart review, Drs. [name] and [name] will investigate the potential violation. If a violation has indeed occurred, Drs. [name] and [name] will report the violation to VA Central IRB.

The facility directors and LSIs of the 6 intervention sites will be notified of the date of the kick off, which will be the start of active implementation for that site and the duration of active implementation for that site (Figure 1).

